**Trial registration:**

Current Controlled Trials ISRCTN20328848. Registered 02 November 2014.

## Background

Mental illness is the largest cause of disability in developed countries, and psychotic disorders (schizophrenia/bipolar disorder) are ranked among the leading causes of total burden of disease and cost of lifetime disability worldwide. In spite of high research activity the mechanisms behind these disorders are still primarily unknown and the effects of available treatments are also limited and mostly palliative.

Most patients experience a relative long period with non-psychotic symptoms before their first psychotic episode characterized by unspecific- and more specific symptom constellations (prodrome/Ultra High Risk (UHR) state). At the onset of psychosis, many have already experienced a loss of cognitive- and psychosocial functioning. We now know that individuals at high risk for psychotic disorders can be identified before this point of time. The present study builds on experiences from the Scandinavian Early Treatment and Intervention in Psychosis (TIPS) study [1,2], where the use of information campaigns and detection teams were instrumental in reducing the duration of untreated psychotic symptoms in the first episode. This reduction was followed by a more benign course of the disorder over ten years of treatment [3]. We here hypothesize that a similar program (Prodromal Detection and Treatment program - PDT) - aimed at identifying and treating help seeking individuals at high risk for developing psychotic disorders will a) significantly increase the number of high risk individuals that get in contact with the relevant services and b) that these individuals will be detected at a very early stage of illness development. After contact the high risk individuals will be allocated to a structured follow-along by a designated case manager or to a graded, multi-modal and primarily psychosocial treatment intervention. Patients will be offered active antipsychotic medication only at imminent risk of conversion to psychosis. We also hypothesize that the multi-modal treatment intervention will significantly reduce the number of persons converting to psychosis, and thus influence the incidence of new cases of first-episode psychosis. The study is designed as a regional multi-center study, involving central research- and clinical psychiatric organizations across the Health Vest region in Southern Norway, with significant international cooperation, and will involve all service levels from general practitioners to specialized psychiatric services. Two Norwegian treatment centers covering a population of 440 000 will collaborate in recruiting prodromal patients to the study: Stavanger and Fonna hospitals. The project organization has additional involvement from the research departments at Bergen University Hospitals and Sykehuset Østfold Hospital for establishing a first-episode psychosis incidence registration as another part of this research initiative. All study enrolled patients will be asked for blood samples and to be a part of the Norwegian NASATS program – Severe Mental Illness, aiming to identify new genetic variants associated with severe mental disorders [4].

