**Methods/Design:**

The study will use a parallel control design comparing the incidence of first episode psychotic disorders between two Norwegian catchment areas with prodromal detection and treatment (Stavanger and Fonna) with two catchment areas without a prodromal intervention program (Bergen and Østfold). The primary aim of the current study is to test the effect of a Prodromal Detection and Treatment program at the health care systems level. The study will investigate: 1) If the combination of information campaigns and detection teams modelled will help in identifying individuals (age 13–65, fulfilling study inclusion criteria) at high risk of developing psychosis early, and 2) If a graded, multi-modal treatment program will reduce rates of conversion compared to the rates seen in follow-along assessments.

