### Aims

The primary aim of the current study is to test the effect of a Prodromal Detection and Treatment program at the health care systems level. The study will investigate; 1) If the combination of information campaigns and detection teams modelled will help in identifying individuals at high risk of developing psychosis early, and 2) If a graded, multi-modal treatment program will reduce rates of conversion compared to the rates seen in follow-along assessments. The study will use the knowledge obtained and the treatment strategies developed from recent experimental studies, and test them out on the health care system level as a proof-of-concept study that intervention in the prodromal phase may lead to a reduction in the development of new cases. The endpoint or main outcome will be the rate of conversion to psychosis. The study will be conducted within a translational approach, comprising clinical and genetic sub-projects as well as an FMRI sub study at Stavanger University hospital, Norway done in close collaboration with health regions in Southern Norway. The aim of these sub-projects is to identify neurobiological indicators of psychosis vulnerability.

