## Methods/Design

### Overall design

The current study will use a health service design modeled after the TIPS study, using the unique possibilities of the Norwegian catchment area based treatment systems. UHR patients from two areas (the catchment areas of Stavanger and Fonna) will be recruited through information campaigns and assessed by low-threshold detection teams. Recruited individuals will, after giving informed consent, receive structured follow-along by a designated case manager, and receive a multi-modal treatment package containing CBT, family work and Omega-III fatty acids and with the possibility for provision of antipsychotic medication only at imminent risk of conversion. Study personnel blind to treatment allocation will confirm this through a separate symptomatic evaluation.

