### Prodromal treatment package

This will be modeled after practices tried out in the TIPS study as well as practices shown to influence risk of conversion in experimental studies and common to existing prodromal centers. The patients will participate in an individual 2 year follow-along containing the following elements:One-to-one monitoring of clinical status, symptom levels (prodromal and psychotic), risk profiles (suicidality, dangerousness), instrumental and social functioning;One-to-one case management to help deal with clinical, familial, social and vocational crises, needs and deficits;Omega-III fatty acids, in the form of 2g fish oils containing approx. 1.5 g Etyl-Eicosapentaeonic Acid/DHA with 80 mgs Vitamin E per day for 12 weeks;Individual cognitive behavioral therapy (CBT) to deal with social/cognitive distortions and deficits and to maintain real world investment (based on the EDIE II study) [49]. They will be offered 26 sessions of CBT within a six months period. The CBT sessions will be based on established cognitive models, be collaborative, problem orientated, formulation driven, normalizing, educational and time-limited with Socratic questioning/ guided discovery;Individuals that experience functional loss will in addition receive single-family psycho-education to inform patients and families about current problems, how to understand and cope with them, especially within the family [50,51];Anti-anxiety agents and anti-depressants will be available if the patient is so symptomatic that they otherwise would be prescribed these agents by their GPs;Antipsychotic medication will be available if the patient either enters the study with any SIPS positive symptom score at the level of 5, or if any positive prodromal symptom score(s) moves from a level of 3 or 4 to a 5. Use will be open labeled based on the patients’ current symptom profile. The type and dose of medication will be reviewed by an independent clinical practice safety monitoring board.

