### Questionnaires and interviews

Participants will be screened with the Structured Interview for DSM-IV (SCID) [52] /(Kiddie SADS for adolescents who are 13–17 years old) and the SIPS at study entrance. All participants will be followed with a symptomatic assessment (SIPS) done monthly for the first six months and then every three months for the last two years. The participant will be evaluated by a designated nevopsychological protocol at baseline, 12 and 24 month follow-up and offered to participate in a fMRI substudy. Assessors will not be part of the treatment teams.

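### The Methods give every high-risk recruit the treatment package, so aim 2's comparison of conversion with follow-along rates has no concurrent comparator

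*Protocol article*

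**What the plan says.** All places are in the protocol article.

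- **Background:** "After contact the high risk individuals will be allocated to a structured follow-along by a designated case manager or to a graded, multi-modal" intervention, which it describes as mainly psychosocial. Follow-along is the alternative to treatment.
- **Overall design:** after consent, recruits "receive structured follow-along by a designated case manager, and receive a multi-modal treatment package containing CBT, family work and Omega-III fatty acids". The same case-manager follow-along is now joined to the package, and no subset is named.
- **Prodromal treatment package:** "The patients will participate in an individual 2 year follow-along containing the following elements". The list covers monitoring, case management, omega-3 for 12 weeks and individual CBT. On CBT: "They will be offered 26 sessions of CBT within a six months period". Only family psycho-education, anti-anxiety or antidepressant drugs, and antipsychotics depend on the patient's state.
- **Aim 2 (Abstract, and Aims in the Background):** "If a graded, multi-modal treatment program will reduce rates of conversion compared to the rates seen in follow-along assessments".
- **Prodromal inclusion and exclusion criteria:** high-risk participants must live in the Stavanger or Fonna catchment areas.
- **Abstract and Background:** Bergen and Østfold have no prodromal programme. They join for first-episode incidence registration.
- **The psychosis incidence study:** the main outcome of the intervention is incidence of psychotic disorders in the participating areas.

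**The concern.** Aim 2 promises a comparison: does treatment lower conversion relative to follow-along? That requires people who are followed without the package. The Background sentence implies that such people exist, but the Methods leave no room for them.

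At stake is how a conversion rate from Stavanger and Fonna may be read. Without a concurrent group, the reference has to come from other studies, and aim 2 neither names one nor says that it would be non-concurrent. Aims also calls the rate of conversion the endpoint or main outcome, so readers will look for this result. A low rate could be reported as a treatment effect when the design cannot separate treatment from the kind of person detected.

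**Working it through.** The argument is structural, so the check sets the statements side by side. The article gives no power or group size for aim 2. Its one power figure (88.9%) is attached to first-episode counts in catchment populations of 750 000 and 440 000 and does not bear on this contrast.

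**Step 1: can both descriptions of care hold?** The Background and Overall design name the same element, follow-along by a designated case manager. One puts *or* between it and the package; the other puts *and*. They cannot both describe the same recruits.

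**Step 2: which one do the Methods support?** The Prodromal treatment package section sides with Overall design. It makes the package part of the two-year follow-along and attaches no condition to omega-3 or CBT. Both Methods sections on care therefore describe a single cohort.

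**Step 3: does the word *graded* supply a follow-along-only subgroup?** No. The graded elements are family work (functional loss), symptomatic drugs (need) and antipsychotics (a SIPS positive symptom score of 5). A patient who needs none of these is still offered CBT and given omega-3.

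**Step 4: could the control areas supply the comparator?** No. High-risk people are not recruited in Bergen or Østfold, so no conversion rate in identified high-risk people arises there.

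**Step 5: what does an outside reference leave open?** The Power calculation gives 20% over two years for non-treated high-risk people, taken from earlier studies, and 10% under active treatment. The planned difference is 20 − 10 = 10 points. Let the true untreated two-year rate in this cohort be 20 − *d* percent and the treatment effect be *t* points. The observed rate is then 20 − *d* − *t*, and the difference from the reference is

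20 − (20 − *d* − *t*) = *d* + *t*.

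Only the sum is observed. With *t* = 0, *d* = 0 gives an apparent effect of 0 points, and *d* = 10 gives 10 points, the whole planned effect. The document gives no value for *d*, so the 0 to 10 range is an assumption that shows what cannot be separated, not an estimate.

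**Step 6: is a non-zero *d* plausible on the document's own account?** Yes. The Background section on conversion reports falling rates in consecutive Melbourne samples, correlated with shorter prodromal symptoms before intake, and adds that changed referral sources may have brought in more false positives. The Background also hypothesises that this programme will reach people at a very early stage.

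**The case against.** The strongest reply is that this is one loose conjunction in a Background section. The Methods agree with each other, the Abstract names a parallel comparison between areas, and a condensed article may leave the source of the follow-along rates to the full protocol. Much of this stands. The two designs are not equally supported, and the single-cohort reading is the better one. But condensing explains missing detail, not opposite statements about who is treated. Accepting the single-cohort reading is also what leaves aim 2 without a comparator.

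Three stronger readings are tempting, and the document does not support them.

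- *A second high-risk arm exists.* A reader might infer this from "Study personnel blind to treatment allocation will confirm this through a separate symptomatic evaluation". That sentence directly follows the provision of antipsychotics at imminent risk of conversion. Being blind to which graded components a patient receives makes sense within one cohort. The active treatment group in the Power calculation can be read as a planning assumption, and the two groups named there are catchment populations.
- *The trial's main comparison is uncontrolled.* A reader might infer this because Aims calls conversion the main outcome. Yet the psychosis incidence section names incidence, and the Power calculation uses transition wording for population counts. Aims may mean that same outcome, which has concurrent control areas.
- *The size of the error can be calculated from published rates.* The article quotes several conversion rates from other studies but adopts none of them as the reference for aim 2. Setting one against another would measure no choice that the plan makes.

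**Conclusion.** The point holds, confined to aim 2. The Background's *or* contradicts two Methods sections. If the Methods govern, the conversion contrast has no concurrent comparator and cannot support a treatment-effect conclusion. In size, none of the planned 10-point difference can be assigned to treatment from this cohort alone, because any shift in background risk adds to it one for one.

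This rests on two assumptions: that the Methods, not the Background, describe what recruits receive, and that no follow-along-only group is defined elsewhere. The between-area incidence comparison is not affected by this point. It should be corrected, but it does not undermine the study's main design.

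**What to change.** **If all recruits get the package, as the Methods say:**

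- In the Background, change *or* to *and* so that it agrees with Overall design and the Prodromal treatment package section.
- In the Abstract and Aims, restate aim 2 in place of "will reduce rates of conversion compared to the rates seen in follow-along assessments". Either report the two-year conversion proportion descriptively with a 95% confidence interval, or contrast it with one reference rate named in advance (for example the Power calculation's 20% at two years) and label that contrast non-concurrent.
- Leave the test of the programme's effect to the between-area incidence comparison.

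**If a follow-along-only group does exist:** correct Overall design and the Prodromal treatment package section so that the package belongs to the treatment group only. Label the contrast observational unless membership is set by chance.

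**In either case:** keep the blinded confirmation of imminent risk and state what the personnel are blind to. The statement "Assessors will not be part of the treatment teams" describes independence, not blinding, and should not replace it.

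**Cost:** a few sentences of text, no new data and no change to the incidence comparison. The real price is a weaker claim: aim 2 becomes descriptive, non-concurrent or observational, which is a change of aim and should be recorded as such.

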
### Rationale

Schizophrenia and other psychotic disorders are serious, costly, and disabling. They typically emerge in late adolescence and early adulthood, a critical phase of neurological, psychological and social development. Even if the number of new cases per year is low (varying between 15 in the TIPS study [1] to −30 per 100 000 per year [5], their early onsets combined with a high risk of chronic symptoms makes these into disorders with a high prevalence (1%).

Many patients display significant impairments already at start of first treatment, and it is known that course and outcome are poorer in patients that come late into treatment. Results from the TIPS study show for the first time that treatment can be initiated significantly earlier in psychotic disorders. This is in turn associated with less severe psychotic symptoms, suicidality and functional disabilities already at first treatment [1,6]. Follow-up after two- and five years in treatment demonstrate long-term advantages in the form of less severe negative symptoms, cognitive deficits, depressive symptoms and global dysfunction [7,8] and for the level of recovery rates up to ten year follow up. Early detection and treatment thus appears to have reduced collateral damage in first psychosis and altered the course and prognosis of the disorder (i.e. achieved secondary prevention). Given these empirical data it is timely to test whether *very* early intervention can actually prevent the development of disorder in individuals at high risk (i.e. primary prevention).

The symptomatic “ultra-high-risk” (UHR) or “prodromal” state has been a part of schizophrenia. In the past decade it has also become a reliably identifiable clinical constellation, with clear power to predict the onset of psychotic disorder (schizophrenia and other psychotic disorders) within the near future. The field of UHR research has the potential to shed light on the development of major psychotic disorders and to alter their course. It also provides a rationale for service provision to those in need of help who could not previously access it and the possibility of changing trajectories for those with vulnerability to psychotic illnesses [9]. These UHR individuals exhibit one or more of the existing prodromal syndromes: The attenuated positive symptom (APS) syndrome and/or the genetic risk and deterioration (GRD) syndrome. The most commonly used instruments to assess prodromal states include those developed in Melbourne (Comprehensive Assessment of At-Risk Mental States (CAARMS)) [10] and New Haven (Structured Interview for Prodromal Syndromes (SIPS) [11]. Because the prodrome is clinical in nature, persons developing these symptoms often seek a familiar clinical caregiver such as a general practitioner, a school counselor or a friend in a healthcare position. Because the UHR state is a relatively rare and new clinical constellation not widely known, recruiting symptomatic, help-seeking persons at risk for psychosis requires active outreach to healthcare-oriented referral sources [12]. This includes educating referral sources about the prodrome, training and maintaining triage staff and conducting rapid, low threshold evaluations of referrals.

### Conversion to psychosis in prodromal samples

In studies using the New Haven/Melbourne UHR criteria, preliminary reports found a 40-50% annual rate of conversion to psychosis of identified individuals [13,14]. This is in line with studies using similar criteria, including studies from Cologne who found a conversion rate of 49 % after 9.6 years [15] and a London based study finding conversion rates of 50% after 2 years [16]. A later study from Melbourne found conversion rates of 34.6% in a sample of 104 UHR subjects identified with the CAARMS [17]. The more recent North American Prodromal Longitudinal Study (NAPLS) - found that 28% of the cases in the study converted to during follow-up. The rate of conversion showed a decelerating trend during the follow-up, with the majority of converters the first two years of the study [18]. At 2.5 year follow up a conversion rate of 29% is reported [19]. In the NAPLS sample, several variables predicted conversion; the most powerful were a diagnosis of schizotypal personality disorder, substance abuse, a recent decline in functioning, unusual thought content and/or suspicion. Recent reports from the prodromal clinic in Melbourne document a falling trend for conversion rates to psychosis among consecutive annual samples between1995-2005 [20]. This declining rate was correlated with a decrease in the duration of prodromal symptoms prior to clinic intake evaluation. Changes in referral sources may also have increased the rate of “false positive” prodromal subjects, i.e. persons who would not subsequently convert to psychosis anyhow. In a recent study by Yung et al., [21] the psychosis conversion rate at 6 month follow-up is 7%. In a recent review article by Simon et al. [22] of 31 studies the reported transition rates varied from 7 to 54% (mean rate = 24%). Follow-up periods ranged from 6 to approximately 40 months. In a meta-study by Fusar-Poli et al. [9] of 2502 patients there was a consistent transition risk, of 18% after 6 months of follow-up, 22% after 1 year, 29% after 2 years, and 36% after 3 years.

### Controlled clinical trials of treatment in the prodrome

In a recent meta-analysis by Stafford et al. [23] 11 included RCT studies made eight comparisons. The authors identified four trials comparing CBT with supportive counseling and monitoring [24-27]. Two trials compared risperidone and CBT with supportive counseling [28,29]. Further on; one study each compared risperidone and CBT with placebo and CBT [28], olanzapine with placebo [30], integrated therapies with supportive counselling [31] integrated therapies with standard treatment [32] Omega-3 fatty acids with placebo [33] and amisulpride plus a needs based intervention with the needs based intervention alone [34]. All these studies measured conversion to psychosis as the primary dependent variable. The studies demonstrate that treatment (psychosocial, pharmacotherapeutic or both) reduce the conversion rate to psychosis. The McGlashan study demonstrated a significant effect in reducing the severity of positive prodromal symptoms, but also major negative side effects in the form of weight gain. Further, there are preliminary reports indicating a possible effect on conversion rates from psychoeducational family work [35]. These recent studies have contributed to the availability for larger datasets, which suggests that transition to psychosis from a high risk mental state could be preventable. Overall, in the meta-analysis by Stafford et al. [23] the five trials of CBT had a moderate effect on transition to psychosis at both 12 and 18 months. In the sensitivity analyses the effect of CBT on transition remained significant at 12 months. There has also been evidence that complex psychosocial interventions could reduce transition or delay onset of psychosis, relative to supportive counseling or treatment as usual. For the study of Omega-3 fatty acids [33] low quality evidence suggests a beneficial effect for a 12 week course of nutritional supplementation compared with placebo.

